### Objectives and hypotheses

There are three objectives in this study, which are:
To test reproducibility of the effectiveness of Health TAPESTRY on health service utilization and physical activity compared to usual care that we found in our initial study [24, 25]To test the feasibility of, and understand the contributing factors to, implementation of the Health TAPESTRY program in six diverse communities across Ontario, CanadaTo determine the value for money of implementing Health TAPESTRY

We hypothesize that results will be reproduced from the first trial evaluation such that Health TAPESTRY will result in a reduction in hospitalizations and an increase in physical activity levels, compared to usual care at 6 months, and will be cost-effective compared to usual care.

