### Sample size

We estimated the sample sizes for both co-primary outcomes physical activity and number of hospitalizations for different effect sizes, based on the initial trial [24, 25], using Bonferroni adjustment [55], with *α* = 0.025 and power = 0.80, using software PASS v19.0.4 [56]. We selected the total sample sizes 488 for physical activity (corresponding to mean difference = 403 and SD = 1441) and 426 for number of hospitalizations (corresponding to mean difference = − 0.14 and SD = 0.47). Using the larger sample size estimate for physical activity and accounting for 20% lost to follow-up, we will require a sample size of 586 participants.

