All analyses will be adjusted for baseline values and sites. All statistical tests will be two-sided and all *p* values will be reported to three decimal places with those less than 0.001 reported as *p* < 0.001. The criterion for statistical significance will be set a priori at alpha = 0.05 and will be adjusted using the Bonferroni method for multiple testing for the co-primary outcomes. There will be no adjustment of alpha for secondary and subgroup analyses as these are exploratory. Analyses will be performed using R v3.6.1 [61].

We will perform sensitivity analyses of the primary outcomes to assess the effectiveness of Health TAPESTRY. We will adopt per-protocol approach to assess the effect of Health TAPESTRY at 6 months. In addition, we will assess the effect of Health TAPESTRY without adjusting for sites and baseline values. We will also use zero inflated Poisson or negative binomial distribution for the count data, depending on the distribution, to assess the robustness of the results.

Implementation: as noted above, implementation is assessed in three ways. For fidelity to the program, sites will be described as either high, medium, or low adherence to the program as intended. The qualitative data centered on implementation will be analyzed using a descriptive thematic analysis [62] and organized using NVivo 12 (QSR 2018) [63]. Transcripts will be independently coded inductively by two reviewers with qualitative analysis experience using open coding. A third reviewer will complete random code checking and provide oversight to ensure trustworthiness of the data. The interview questions will serve as the coding guide for the first few transcripts. The three reviewers will discuss and create a formal coding structure and review it regularly as more transcripts are coded to begin to collapse codes into over-arching themes. The themes will be aligned with the NPT constructs [26, 27].

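### Plain Bonferroni for the two co-primary outcomes is valid but gives up power that Holm would recover at the same 5% family-wise error and the same sample size

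*Protocol article*

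**What the plan says.** The Data analysis section of the protocol article fixes the testing rule. "The criterion for statistical significance will be set a priori at alpha = 0.05", and this level "will be adjusted using the Bonferroni method for multiple testing for the co-primary outcomes". It also states "All statistical tests will be two-sided". With two co-primary outcomes, each is therefore tested at two-sided 0.025.

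The Sample size section is consistent with this. Each outcome is sized on its own, with alpha = "0.025 and power = 0.80, using software PASS v19.0.4". The selected totals are "488 for physical activity (corresponding to mean difference = 403 and SD = 1441") and "426 for number of hospitalizations" (mean difference −0.14, SD 0.47). The larger total is carried forward and raised to 586 for 20% loss to follow-up.

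Under Objectives and hypotheses the expectation is that "Health TAPESTRY will result in a reduction in hospitalizations and an increase in physical activity levels, compared to usual care at 6 months". The article does not say whether one or both co-primary results must be significant for a claim, and it gives no correlation between the two outcomes.

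**The concern.** Bonferroni holds each test at 0.025 whatever the other test shows. Once one co-primary null hypothesis has been rejected, only one remains that could be falsely rejected, and it can be tested at the full 0.05 without exceeding 5% overall. Holm uses this step and Bonferroni does not. A result with, say, p = 0.01 on one outcome and p = 0.04 on the other would count as one significant outcome under the plan and two under Holm, from the same data and with the same error guarantee.

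What is at stake is power. The trial exists to see whether two earlier findings recur, and the named method makes it more likely than necessary that a real effect on the second outcome is declared not significant.

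**Working it through.** **Inputs.** From Sample size: two-sided alpha 0.025, power 0.80; physical activity difference 403, SD 1441; hospitalizations difference 0.14, SD 0.47; totals 488 and 426. From Randomization and blinding: 1:1 allocation. Assumed, because the article does not give it: correlation 0 between the two test statistics (in the direction of benefit), with a range up to 0.5.

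**1. Reproduce the plan's figures.** Per arm, n = 2 (z₀.₉₈₇₅ + z₀.₈₀)² (SD/difference)², with z₀.₉₈₇₅ = 2.2414 and z₀.₈₀ = 0.8416, so the squared sum is 9.505.
- Physical activity: 2 × 9.505 × (1441/403)² = 2 × 9.505 × 12.785 = 243.05, rounded up to 244 per arm, 488 in total. This matches exactly.
- Hospitalizations: 2 × 9.505 × (0.47/0.14)² = 2 × 9.505 × 11.270 = 214.25, rounded up to 215 per arm, 430 in total. The stated 426 is within 1% of this.

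**2. Power of each test at 244 per arm.** The expected z statistic is (difference/SD) × √(244/2).
- Physical activity: 0.27967 × 11.045 = 3.089. Hospitalizations: 0.29787 × 11.045 = 3.290.
- Power at 0.025 is Φ(expected z − 2.2414); at 0.05 it is Φ(expected z − 1.9600).

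| Outcome | Power at 0.025 | Power at 0.05 |
|---|---|---|
| Physical activity | 0.8017 | 0.8706 |
| Hospitalizations | 0.8528 | 0.9083 |

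Hospitalizations exceed 80% because 488 is more than that outcome needs.

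**3. Power of each outcome under Holm.** An outcome is significant if its p ≤ 0.025, or if its p lies between 0.025 and 0.05 and the other p ≤ 0.025. Under independence:
- Physical activity: 0.8017 + (0.8706 − 0.8017) × 0.8528 = 0.860.
- Hospitalizations: 0.8528 + (0.9083 − 0.8528) × 0.8017 = 0.897.

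**4. Chance that both are significant.**
- Bonferroni: 0.8017 × 0.8528 = 0.684.
- Holm (both p ≤ 0.05 and at least one ≤ 0.025): 0.8017 × 0.9083 + 0.8706 × 0.8528 − 0.6837 = 0.787.

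The chance of at least one significant outcome is the same under both methods, because Holm's first step is the Bonferroni test: 0.8017 + 0.8528 − 0.6837 = 0.971.

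**5. Sensitivity of the chance of showing both.**

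| Scenario | Bonferroni | Holm | Gain |
|---|---|---|---|
| 488 analysed, correlation 0 | 68.4% | 78.7% | 10.3 points |
| 488 analysed, correlation 0.5 | 72.4% | 80.9% | 8.5 points |
| 468 analysed, correlation 0 | 65.5% | 76.4% | 10.8 points |

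The third row takes 586 recruited less 20%: 586 × 0.8 = 468.8, so about 468. Gains were computed before rounding.

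**6. Error control.** If both nulls are true, Holm makes an error only if the smaller p is at or below 0.025, which has probability at most 2 × 0.025 = 0.05. If only one null is true, it can be falsely rejected only if its own p is at or below 0.05. The family-wise error is therefore at most 5% in every case, as with Bonferroni.

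**The case against.** The best defence is that nothing here is wrong. Sizing at 0.025 and testing at 0.025 agree, family-wise error is controlled, and Bonferroni is a common and transparent choice. That stands: this is a point about efficiency, not validity. It is also not something left to an analysis plan that is not shown, because the article names the method itself.

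A reader might go further and infer from Objectives and hypotheses that the trial succeeds only if both outcomes are significant, so that 80% overstates its power. The article does not support this. The sentence lists expected effects, and it goes on to include cost-effectiveness, which is assessed with acceptability curves and not by a pass/fail test. Splitting alpha is the usual structure for two separate claims. Sample size gives 80% as the input to each of two separate calculations and never calls it the power for both. Two outcomes at exactly 80% would in any case give 0.80 × 0.80 = 64% for both under independence; the 68% arises because hospitalizations have about 85% at 488. If both were truly required, no adjustment would be needed: each could be tested at 0.05, giving 0.8706 × 0.9083 = 79.1%.

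Two further objections stand in part. The powers come from the unadjusted two-means inputs, whereas the plan uses linear and count regressions adjusted for baseline and site, with multiple imputation, so realised power may differ. And recruitment was already open, with outcome data collectors unblinded, so a change to the primary testing rule needs a formal record.

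**Conclusion.** The point holds as an improvement that costs nothing in type I error or participants, whether the two outcomes are read as separate claims or together. At 488 analysed, Holm adds about 6 percentage points of power for physical activity (80% to 86%) and about 4 for hospitalizations (85% to 90% when rounded; 85.3% to 89.7%). It adds about 10 points to the chance of showing both (68% to 79%).

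The sizes rest on the protocol's two-means inputs and on independence of the outcomes; for the chance of showing both, the gain is still 8.5 points at correlation 0.5. That Holm never rejects less than Bonferroni rests on none of these assumptions. The point does not show a flaw in error control, a misstated power, or a requirement that both outcomes succeed.

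**What to change.** In Data analysis, name Holm instead of Bonferroni for the two co-primary tests: compare the smaller p-value with 0.025 and, only if it is significant, compare the other with 0.05. Make the change by a dated amendment before outcome data are analysed. No both-required success rule needs to be added.

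The calculation in Sample size can stay at 0.025 per outcome; it is then conservative for the test actually used. No additional data or participants are needed.

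The cost is the amendment itself and a small loss of simplicity: simultaneous confidence intervals that match Holm are harder to construct than those that match Bonferroni. The planned reporting is not affected, because Data analysis specifies ordinary 95% intervals for both co-primary outcomes.

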### Data collection

Outcome data collection will occur through the structured surveys via the TAP-App, from the electronic medical record (EMR), program records, and focus groups/interviews (Table 3). Health care utilization outcomes will be measured during the 6-month period prior to study enrollment (i.e., before baseline) and during the 6-month study period. For the EMR data extraction, all researchers will undergo training and use a standardized data abstraction form that has been pilot tested. We will calculate agreement scores between auditors for a subset of the sample.

**Table 3 Tab3:** Summary of outcomes, measures, and analysis plan using the RE-AIM framework

RE-AIM element	Outcome	Outcome measure; *source*	Data collection time point	Analysis
Reach *The reach of the intervention into the target population*	Participants	Proportion of eligible patients who consent; *self-report*	T_0_	Simple proportions and range across sites
	Sample characteristics	Demographics including chronic conditions; *self-report*, *EMR*	T_0_	Simple proportions and range across sites
	Volunteer visits	Number of volunteer visits; *program records*	T_6_	Frequency count across sites
Effectiveness *Positive and adverse effects of the intervention*	Hospitalizations*	Number of hospitalizations; *EMR*	T_0_, T_6_	Poisson regression or negative binomial regression
	Physical activity*	Total minutes spent doing moderate, vigorous, activity and walking (IPAQ); *self-report*;	T_0_, T_6_	Multiple linear regression
	Sitting	Hours sitting (IPAQ); *self-report*	T_0_, T_6_	
	Patient enablement	PEI; *self-report*	T_0_, T_6_	
	Quality of life	EQ 5D-5L; *self-report*	T_0_, T_6_	
	Treatment burden	MTBQ; *self-report*	T_0_, T_6_	
	Disease burden	DBMA; *self-report*	T_0_, T_6_	
	Emergency room or urgent care	Number of emergency room or urgent care visits; *EMR*	T_0_, T_6_	Poisson regression or negative binomial regression Poisson regression or negative binomial regression
	Falls	Number of falls; *EMR*	T_0_, T_6_	
	Medications	Number of medications; *EMR*	T_0_, T_6_	
	Primary care visits	Number of primary care visits; *EMR*	T_0_, T_6_	
	Negative effects	Unmet expectations; *self-report*	T_6_	Descriptive analysis across sites
		Labeling effect of screening tools; *self-report*	T_6_	
		Number and nature of serious adverse events; *EMR*	T_6_	

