### Data analysis

The results will be reported according to the CONSORT extension for pragmatic randomized trials [57] and non-pharmacological interventions [58]. The mean (standard deviation) or median (first quartile, third quartile) for continuous variables, depending on the distribution, and count (percent) for categorical variables will be calculated. The description of the data analysis approach below is separated based on the RE-AIM framework for effectiveness and implementation. Note that for reach, adoption, and maintenance, the analysis approach is found in Table 3.

Effectiveness: the effectiveness of Health TAPESTRY will be assessed at 6 months. We will adopt intention-to-treat (ITT) as the primary analysis approach. Multiple imputation approach using chained equations will be used to impute the missing data [59]. We will consider the fraction of missing information and determine the number of imputations needed using the two-stage approach suggested by Hippel [60]. The pooled effect estimates along with 95% confidence intervals will be reported. The co-primary outcome of a number of hospital admission will be analyzed using the Poisson regression or negative binomial regression depending on the distribution. The incidence rate ratio along with 95% confidence interval will be reported. And the co-primary outcome physical activity will be analyzed using the multiple linear regression. The mean difference between intervention and control group along with 95% confidence intervals will be reported. The continuous outcomes (sitting, patient enablement, quality of life, treatment and disease burden scores) and the count secondary outcomes (number of falls, number of primary care visits, number of emergency room or urgent care visits, number of medications) will be analyzed using the multiple linear and Poisson regression or negative binomial regression, respectively. The mean difference and incidence rate ratio along with 95% confidence intervals will be reported for continuous and count outcomes respectively.

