To assess the third part of “implementation” of RE-AIM, an economic evaluation of the trial will be conducted in accordance with Canadian and international guidelines for the conduct of economic evaluations of healthcare programs [64–66]. This 6-month trial-based economic evaluation will compare Health TAPESTRY versus usual care in terms of costs and quality-adjusted life years (QALYs) from a public payer perspective. To calculate costs associated with the intervention, healthcare resource utilization (e.g., physician visits, emergency room visits, hospital visits) captured in the EMR (Table 3) will be multiplied by their respective unit costs. Cost associated with the delivery of Health TAPESTRY will be derived from trial data. The volunteer organizations will track front-line program costs (e.g., training, transportation costs for home visit) and research team will monitor all other costs (e.g., development of material, personnel time). Every site may not implement the program exactly the same in which case any cost differences will be accounted for. To measure the impact of Health TAPESTRY and usual care on health-related quality of life, all participants will answer the EQ-5D-5L at baseline and 6 months (Tables 2 and 3). The Canadian algorithm will be used to derive the EQ-5D health utility scores [67]. QALYs will be calculated by the weighted EQ-5D health utility scores by time spent in health state using an area under the curve approach.

Differences in costs and QALYs will be determined using parametric or non-parametric tests as appropriate, and bootstrap techniques will be used to deal with sampling uncertainty and generate 95% confidence intervals [68]. Cost-effectiveness acceptability curves will be used to present the probability of Health TAPESTRY to be cost-effective at different willingness-to-pay thresholds (e.g., $50,000/QALY gained; $100,000/QALY gained) [64, 66]. Several sensitivity analyses will be conducted to explore the impact of certain assumptions (e.g., cost of implementing Health TAPESTRY) on the results. Missing data will be imputed using multiple imputations [69]. The results will be reported as per the Consolidated Health Economic Evaluation Reporting Standards (CHEERS) guidelines [70].

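### Half of each QALY is the baseline utility, yet the economic analysis names no baseline adjustment, and it is unclear whether the general adjustment rule covers it

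*Protocol article*

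**What the plan says.** The economic evaluation is the third part of the Implementation text in the Data analysis section of the protocol article. On utility measurement it says that "all participants will answer the EQ-5D-5L at baseline and 6 months". On construction: "QALYs will be calculated by the weighted EQ-5D health utility scores by time spent in health state using an area under the curve approach". On the comparison of arms: "Differences in costs and QALYs will be determined using parametric or non-parametric tests as appropriate". Bootstrap 95% confidence intervals and acceptability curves follow, with example thresholds ("e.g., $50,000/QALY gained; $100,000/QALY gained"). No covariate appears in that text.

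Earlier in the same section, after the effectiveness models and before the Implementation text, the article states: "All analyses will be adjusted for baseline values and sites". The section opens by explaining its layout: "The description of the data analysis approach below is separated based on the RE-AIM framework for effectiveness and implementation".

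The Data collection section shows that the material for a baseline cost exists: "Health care utilization outcomes will be measured during the 6-month period prior to study enrollment".

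**The concern.** With two measurements, the area under the curve gives the pre-intervention utility the same weight as the 6-month utility. A two-group test on that quantity treats the baseline half as if it were outcome. Any chance difference between arms at T0 then enters the QALY difference, and the variance of T0 utility enters its standard error. Both can be removed by conditioning on a value that the trial already records.

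The plan may also treat the same scores in two ways. As a secondary effectiveness outcome, EQ-5D-5L is analysed by multiple linear regression with baseline adjustment. The QALY built from those scores may be compared without it. Value for money is one of the three stated objectives, and cost-effectiveness is part of the stated hypothesis, so the precision of this comparison matters.

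**Working it through.** **The plan's own figure.** The article gives no SD, precision or power for QALYs or costs. The only figure to borrow is the number analysed. With mean difference 403, SD 1441, two-sided alpha 0.025 and power 0.80, the two-means formula gives 244 per arm, 488 in total, which matches the Sample size section. I use 244 per arm below.

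**Assumed inputs, not in the article.** Utility SD s = 0.20, equal at both visits; T0-T6 utility correlation r of 0.3 to 0.7; cost SD of $2,000 to $15,000; correlation of prior with follow-up cost rc of 0.2 to 0.4; cost and QALY independent.

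**QALY per person.** 0.5 years x (u0 + u6)/2 = 0.25 x (u0 + u6).

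**Variance per person.**
- Unadjusted: 0.0625 x s² x 2(1 + r).
- Adjusted for u0: 0.0625 x s² x (1 - r²).
- Ratio of variances: (1 - r)/2. Ratio of standard errors: sqrt((1 - r)/2), whatever the value of s.

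| r | SE ratio | SE unadjusted (s = 0.20) | SE adjusted |
|---|---|---|---|
| 0 | 0.71 | 0.0064 | 0.0045 |
| 0.3 | 0.59 | 0.0073 | 0.0043 |
| 0.5 | 0.50 | 0.0078 | 0.0039 |
| 0.6 | 0.45 | 0.0081 | 0.0036 |
| 0.7 | 0.39 | 0.0084 | 0.0032 |

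Example at r = 0.6: unadjusted variance 0.0025 x 3.2 = 0.0080, so SE = sqrt(0.0080 x 2/244) = 0.0081. Adjusted variance 0.0025 x 0.64 = 0.0016, so SE = sqrt(0.0016 x 2/244) = 0.0036. A simulation with 244 per arm and 4,000 runs gave SE ratios of 0.51 at r = 0.5 and 0.39 at r = 0.7, in line with the formula.

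**Effect of a chance T0 gap.** A gap d in mean T0 utility shifts the unadjusted QALY difference by 0.25 x (1 + r) x d. One standard error of the T0 gap is 0.20 x sqrt(2/244) = 0.018. At r = 0.6 the shift is 0.25 x 1.6 x 0.018 = 0.0072 QALY, or 0.0072 x $50,000 = $360 per person. For scale, a true 0.03 utility effect at 6 months gives 0.25 x 0.03 = 0.0075 QALY.

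**Costs.** Adjusting for prior cost multiplies the cost SE by sqrt(1 - rc²): 0.98 at rc = 0.2 and 0.92 at rc = 0.4, a reduction of about 2% to 8%.

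**Net benefit.** With threshold W, the variance is W² x Var(QALY) + Var(cost). For example, take W = $50,000, r = 0.5, cost SD $4,000 and rc = 0.2:
- Unadjusted: 0.0075 x 2.5 x 10⁹ + 16.00 x 10⁶ = 34.75 x 10⁶.
- Adjusted: 0.001875 x 2.5 x 10⁹ + 0.96 x 16 x 10⁶ = 20.05 x 10⁶.
- SE ratio: sqrt(20.05/34.75) = 0.76.

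Over cost SDs of $2,000 to $15,000, r of 0.5 to 0.7 and rc of 0.2 to 0.4, the ratio runs from 0.51 to 0.95 at $50,000 per QALY and from about 0.43 to 0.89 at $100,000.

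**The case against.** **The article has an adjustment rule.** Read literally, it covers every analysis, and its neighbours (two-sided tests, software) also read as general rules. This stands in part: one cannot say that the plan excludes adjustment from the economic evaluation. But the section separates effectiveness from implementation, and the rule falls in the effectiveness part. The economic text restates imputation and 95% intervals for itself but not adjustment. Even the literal reading leaves a gap. A QALY accrued over follow-up has no baseline value of its own, so the covariate has to be named.

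**The wording on tests does not forbid covariates.** A bootstrapped regression coefficient could be fitted under it, and a condensed article may leave model details to a fuller plan. This too stands in part. A reader might infer that the plan commits to plain two-group tests, and the text does not go that far. It does name the method of comparison, though, and that method sits badly with the adjustment rule, above all if a standard non-parametric test is used.

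**Randomization protects the comparison.** This stands. The unadjusted difference is unbiased, and its bootstrap interval already allows for chance imbalance at T0. A one-SE gap is ordinary sampling error.

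**Cost variance dilutes the gain.** This stands. Take the article's hospitalization SD of 0.47 and an assumed $7,000 to $15,000 per admission: admissions alone give a cost SD of about $3,300 to $7,050. With r = 0.6, s = 0.20 and rc = 0.3, the net-benefit SE ratio at $50,000 is then about 0.67 to 0.84.

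**Conclusion.** The point holds as one of efficiency and clarity. The economic text fixes a QALY that is half baseline utility, names tests without covariates, and is not plainly covered by the adjustment rule. If run unadjusted, the QALY difference has a standard error larger than necessary: the adjusted SE would be 0.59, 0.50 or 0.39 of it for r = 0.3, 0.5 or 0.7. These ratios assume equal utility SD at the two visits and a correlation that the article does not give. The direction does not depend on r, since even r = 0 gives 0.71.

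Two stronger readings are not supported. One is that the whole cost-utility result is about half as precise as it could be. That figure belongs to the QALY difference at r near 0.5. For net benefit the ratio is about 0.43 to 0.95 under assumed costs, and prior-cost adjustment alone trims the cost SE by only about 2% to 8%. The other is that the result would be biased. Under randomization it is not; the loss is precision, plus sensitivity to whatever T0 imbalance happens to occur.

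**What to change.** In the economic part of the Data analysis section, replace the tests with bootstrapped regression:
- QALYs on arm, T0 EQ-5D-5L utility and site.
- Costs on arm, cost in the 6 months before enrolment, and site.
- Each participant's cost and QALY resampled together, so that their correlation is kept.
- The adjusted differences fed into the acceptability curve, with the unadjusted comparison kept as a sensitivity analysis.

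Then align the general adjustment sentence, stating that it covers the economic evaluation and pointing to these covariates. This takes a sentence or two of text. It needs no new data and no further participants, since T0 utility and pre-enrolment utilization are already collected. The extra analysis time is negligible.

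### The economic evaluation names no baseline adjustment for costs or QALYs, although half the weight of the 6-month QALY is the baseline EQ-5D score; adjusting would sharpen the QALY result considerably at no data cost.

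*Protocol article*

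**What the plan says.** The economic evaluation serves objective 3, value for money. The Data analysis section of the protocol article files it under the implementation element of RE-AIM. Its relevant statements are:

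- Comparison: "Differences in costs and QALYs will be determined using parametric or non-parametric tests as appropriate".
- Uncertainty: "bootstrap techniques will be used to deal with sampling uncertainty and generate 95% confidence intervals".
- QALY construction: "QALYs will be calculated by the weighted EQ-5D health utility scores by time spent in health state using an area under the curve approach".
- Utility measurement: "all participants will answer the EQ-5D-5L at baseline and 6 months".

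None of these names a model or a covariate. Earlier in the same section, after the effectiveness models and before the implementation part, stands a general rule: "All analyses will be adjusted for baseline values and sites". On available covariates, the Data collection section says: "Health care utilization outcomes will be measured during the 6-month period prior to study enrollment", and again over the 6 study months.

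**The concern.** With two utility measurements half a year apart, the QALY contains the baseline score, which the programme cannot change. If the arms differ at baseline by chance, a plain comparison carries part of that difference into the incremental QALY and so into the cost-effectiveness result. Even when the arms are well balanced, the baseline component adds sampling variance that regression on the baseline score would remove. A 6-month QALY difference is likely to be small, so this noise can be as large as the effect sought.

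The effectiveness part gives quality of life, measured with the same EQ-5D-5L, a multiple linear regression with baseline adjustment. The economic part gives QALYs built from that instrument only a choice of tests. Whether the general adjustment rule was meant to carry over cannot be settled from the text.

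**Working it through.** **Plan's own figure.** The economic evaluation states no numerical target. The trial's governing figure does reproduce: for physical activity, a difference of 403, SD 1441, two-sided alpha 0.025 and power 0.80 give 2 × (2.241 + 0.842)² × (1441/403)² ≈ 243.1, so 244 per arm and 488 in total, as stated. I use 488 (244 per arm) and the recruitment target of 586 (293 per arm) only as sample sizes below.

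**Inputs from the article.** EQ-5D-5L at 0 and 6 months; area-under-the-curve QALY; 1:1 allocation; willingness-to-pay thresholds of $50,000 and $100,000 per QALY.

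**Assumptions, not in the article.** The utility SD is equal at both times. SD and the correlation r between baseline and 6-month utility are varied over ranges.

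**Step 1: the QALY.** Over 0.5 year, QALY = 0.5 × (u0 + u6)/2 = 0.25·u0 + 0.25·u6.

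**Step 2: pass-through.** A baseline difference d adds 0.25·d directly and 0.25·r·d through the 6-month score, which makes 0.25(1 + r)·d in all. That is 0.35d, 0.40d and 0.45d for r = 0.4, 0.6 and 0.8.

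**Step 3: size of an ordinary imbalance.** One standard error of the baseline difference is SD × √(2/n) with n per arm.

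| n per arm | SD assumed | r assumed | one-SE imbalance in utility | shift in incremental QALY | at $50,000 per QALY |
|---|---|---|---|---|---|
| 293 | 0.15–0.20 | 0.4–0.8 | 0.012–0.017 | 0.0043–0.0074 | $217–$372 |
| 244 | 0.15–0.25 | 0.5–0.8 | 0.014–0.023 | 0.0051–0.0102 | $255–$509 |

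At $100,000 per QALY the second row becomes $509–$1,019. For scale, an illustrative true gain of 0.03 in utility at 6 months is worth 0.25 × 0.03 = 0.0075 QALY.

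**Step 4: precision.** The unadjusted QALY variance is proportional to 2 + 2r. After regression on u0 it is proportional to 1 − r². The SE ratio is √[(1 − r²)/(2 + 2r)] = √[(1 − r)/2].

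| r | SE ratio | reduction in SE |
|---|---|---|
| 0.4 | 0.548 | 45% |
| 0.6 | 0.447 | 55% |
| 0.8 | 0.316 | 68% |

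These ratios do not depend on SD or sample size. In absolute terms, with 244 per arm, SD 0.15–0.25 and r 0.5–0.8, the SE falls from 0.0059–0.0107 to 0.0020–0.0049.

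**Step 5: simulation.** I take 5,000 simulated trials with no effect, N = 488, SD 0.20 and r = 0.6. The unadjusted QALY difference had slope 0.399 on the baseline difference (formula: 0.400); the adjusted one had slope −0.001. The empirical SEs were 0.0080 and 0.0037. Both estimators centred on zero.

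**Step 6: scope of the adjustment rule.** The Data analysis section says its description is split into effectiveness and implementation. The adjustment sentence is in the former and the economic evaluation in the latter. The economic text also sets its own imputation, interval and comparison rules instead of inheriting the earlier ones. The natural reading is that the adjustment rule covers effectiveness only, but its wording does not exclude the economic analysis.

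**The case against.** Several counter-arguments have force.

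- **A reader might infer that the plan commits to unadjusted two-group tests.** It does not say so. A test of an arm coefficient in a regression is also a parametric test, and the general adjustment sentence is worded to cover all analyses. What stands is that the economic text is silent on covariates and does not fit clearly with that sentence.
- **A reader might infer that the cost-effectiveness result would be biased.** It would not. Randomisation keeps the unadjusted difference unbiased, and a bootstrap of it already reflects chance imbalance, so its interval is valid, only wide. The loss is one of precision, together with sensitivity to whatever imbalance occurs.
- **A reader might infer that a rank test would corrupt the acceptability curve.** A rank-test p-value does not feed that curve; the article assigns sampling uncertainty to the bootstrap. The point that remains is narrower: a rank test does not address the difference in means on which the cost-effectiveness result rests.
- **The containment argument does not extend to costs.** Study-period costs do not include prior-period use. Adjustment helps there only as far as the two are correlated, and no figure can be given from the article.
- **This is a condensed article.** A full protocol or health-economic plan may list covariates. That limits how firmly the gap can be asserted. However, the article does state a comparison method for this objective, and that statement would benefit from amendment in any case.

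**Conclusion.** The point holds as a missed improvement and an unclear scope, not as a demonstrated error. The economic text names a comparison method without baseline adjustment, and the general adjustment rule does not clearly extend to it. For QALYs the consequence is material: 0.25(1 + r) of any chance baseline difference enters an unadjusted incremental QALY, and adjustment would cut its standard error by about 45% to 68% for r of 0.4 to 0.8. A one-SE imbalance moves the result by roughly 0.004 to 0.010 QALY across the ranges examined, comparable with the 0.0075 QALY from a 0.03 utility gain. All these sizes rest on assumed utility SD, correlation and equal variances. For costs the gain is real only through correlation with prior use and is not quantified. Neither co-primary outcome is affected.

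**What to change.** In the economic evaluation text of the Data analysis section, replace the sentence on tests with a statement that:

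- the incremental QALY is estimated by regression on arm, baseline EQ-5D utility and site;
- the incremental mean cost is estimated by regression on arm, health care use or cost in the 6 months before enrolment, and site;
- these adjusted mean differences are computed within the multiple imputation and the bootstrap that feed the acceptability curve;
- any rank test of costs or QALYs is descriptive only.

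This also settles whether the general adjustment rule applies to the economic analysis. The choice of regression family for costs and the handling of couples in resampling are separate matters and not part of this change. The cost is revised wording and modest extra analysis code; both covariates are already in the data collection plan.
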